## Methods and analysis

### Overview

AZA-PD is a randomised, double-blind, placebo-controlled trial of azathioprine in early PD that aims to provide ‘proof of concept’ that a peripherally acting immunosuppressive drug can slow clinical disease progression. The trial will investigate whether the drug has an effect on disease course over 12 months of treatment and whether this is maintained over 6 months of subsequent follow-up. Sixty participants will be recruited and randomised 1:1 to receive active treatment or placebo. Clinical assessments will be performed at baseline, 6 months, 12 months and 18 months (6 months postcompletion of treatment), with rigorous safety monitoring. In addition, the trial aims to demonstrate ‘proof of mechanism’ by evaluating the impact of azathioprine on blood, CSF and neuroimaging parameters of immune activation in the trial population and determining the relationship between these parameters and clinical measures of disease progression.

The trial timeline is summarised in figure 1.

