#### Sample size calculation

The treatment effect size is unknown and therefore cannot be used to inform sample size calculations. A sample size of 60 has been selected pragmatically based on feasibility of recruitment.

However, longitudinal clinical data from the Incidence of Cognitive Impairment in Cohorts with Longitudinal Evaluation-PD (ICICLE-PD) cohort study provides some idea of an anticipated effect size for the primary outcome measure. ICICLE-PD patients were stratified by cytokine profile. Those with a ‘proinflammatory’ profile (n=32) had a more rapid symptom progression, with mean (SD) annualised change in MDS-UPDRS gait/axial score of 1.95 (1.92). In the subgroup with an ‘anti-inflammatory’ cytokine profile (n=26), mean (SD) annualised change in MDS-UPDRS gait/axial score was 0.72 (1.40).^12^ The corresponding between-group difference of 1.2 points is equivalent to a standardised effect size (Cohen’s d) of 0.73. The magnitude of this effect, which equates to a 4% change on the 28-point gait/axial MDS-UPDRS subscale, would be clinically significant. For comparison, the estimated minimum clinically important change on the full 132-point MDS-UPDRS motor scale is ≈2% (2.5 points).^43^ Furthermore, the axial-gait items of the MDS-UPDRS are those with the greatest impact on quality of life.^42^

As this is an early-phase proof of concept trial, it is important to maximise the chances of continuing development if the treatment is genuinely effective, and thus a significance level of 25% under a one-sided test will be used. If the treatment effect is a 2% change (0.37 standardised effect), the design has 78% power, and for a 4% change (0.73 standardised effect), the design has 99% power.

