## Data analysis

Trial data will be transferred from paper case report forms (CRFs) to the electronic trial database, where it will be anonymised, but with preserved linkage records. Patient-identifiable data (PID) will be stored on a password-protected database within the Secure Data Hosting Service (SDHS) hosted by the University of Cambridge, with access granted only to relevant members of the trial team. PID will be kept for 5 years following the end of the trial, as per regulatory requirements. Participant consent will be specifically sought for data/sample sharing with our collaborators and use of remaining biological samples in future ethically approved research.

Data will be analysed on an ‘intention to treat’ basis, with further ‘per protocol’ analysis in participants with at least 80% compliance with trial medication. All endpoints will be summarised and broken down by treatment group and time point, where relevant. Mean, median, SD and minimum/maximum will be used for continuous endpoints and frequency tables for categorical or binary endpoints. Equivalent box and whisker plots or stacked bar charts will be produced for continuous and categorical endpoints, respectively.

The primary analysis will estimate the difference between treatment groups in terms of the primary endpoint. An analysis of covariance (ANCOVA) model will be fitted adjusting for baseline MDS-UPDRS gait/axial score, gender, LEDD and age. Treatment effect estimates, SEs, CIs (95% and 40% levels) and one-sided p values will be provided. A one-sided p value less than 25% will be regarded as statistically significant. Similar comparative analyses will be produced for other time points of the MDS-UPDRS gait/axial score and exploratory endpoints, using ANCOVA for continuous endpoints or logistic regression for categorical or binary endpoints.

Longitudinal data will use a mixed effect model repeated measurements (MMRM) analysis to include an unstructured patient-level random effect for nominal visit, visit and visit–treatment interaction fixed effects at visits post-baseline, with adjustment for baseline covariates. To assess the slope of change over time, the longitudinal data will be analysed using a similar MMRM but with a fixed effect of time from randomisation as a continuous, rather than nominal covariate, with a treatment–time interaction to compare treatment groups and patient-level random effect for slope, with adjustment for baseline covariates.

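### The supportive slope model has one straight line and one treatment-time interaction with no break at 12 months; if month 18 is included, as the text naturally reads, the on-treatment slope difference is diluted unless the arms keep diverging after treatment stops

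*Protocol article*

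**What the plan says.** The Overview of the protocol article sets the visit times: "Clinical assessments will be performed at baseline, 6 months, 12 months and 18 months (6 months postcompletion of treatment"). It asks two things: whether the drug affects disease course over 12 months of treatment, and "whether this is maintained over 6 months of subsequent follow-up". Table 1 schedules the MDS-UPDRS at baseline, Day 182, Day 365 and Day 547.

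The Data analysis section describes three layers of analysis for the gait/axial score:

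- An ANCOVA of the 12-month change, which is primary, with similar comparisons at other time points.
- An MMRM with nominal visit and visit-by-treatment effects at the post-baseline visits.
- A similar MMRM for the slope, with "a fixed effect of time from randomisation as a continuous, rather than nominal covariate", one treatment-time interaction to compare the arms and a patient-level random slope.

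The slope model is applied to the longitudinal data. The article gives it no time window, no change point and no separate off-treatment slope.

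**The concern.** A single interaction forces the between-arm difference to be a straight line in time from randomisation. Treatment stops at 12 months, so a straight line to 18 months requires the drug to go on slowing progression at the same rate after it is withdrawn. That is a stronger condition than the maintained benefit the Overview asks about. A benefit that is fully held after stopping means parallel arms from month 12, and the model does not fit even that favourable course.

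What is at stake is the reading of the one analysis that is expressed as a rate of change. The trial aims to show that the drug can slow progression. A diluted slope could seem to contradict a positive 12-month result, and it would merge the on-treatment question and the persistence question into one number.

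**Working it through.** **Inputs.** From Sample size calculation: annualised gait/axial change of 1.95 (SD 1.92) in the proinflammatory group and 0.72 (SD 1.40) in the anti-inflammatory group; "a significance level of 25% under a one-sided test will be used". From Overview: "Sixty participants will be recruited and randomised 1:1 to receive active treatment or placebo", taken as 30 per arm, and visits at 0, 0.5, 1 and 1.5 years.

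**The plan's own figure first.** The difference is 1.95 − 0.72 = 1.23 points. The average SD is √((1.92² + 1.40²)/2) = 1.68, so d = 1.23/1.68 = 0.73, as stated. Power = Φ(d√(30/2) − 0.674):

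- d = 0.37: Φ(1.433 − 0.674) = 77.6%. The article says "If the treatment effect is a 2% change (0.37 standardised effect), the design has 78% power".
- d = 0.73: Φ(2.827 − 0.674) = 98.4%, against a stated 99%.

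Both agree to within a point. They concern the 12-month comparison; the article states no power for the slope model.

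**Set-up for the slope.** Let D be the on-treatment slope difference per year, in the direction of benefit, and assume it is constant over the 12 months. In units of D, the between-arm difference is 0 at baseline, 0.5 at month 6, 1 at month 12 and c at month 18. The documents do not give c, so it is varied: 1.5 (same divergence continues), 1 (gap maintained), 0.5 (half lost), 0 (all lost).

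**Fitted interaction as a share of D.** The article does not say how the intercept is handled, so three versions are shown.

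1. Post-baseline visits, arms equal at time 0: Σty/Σt² = (0.25 + 1 + 1.5c)/(0.25 + 1 + 2.25) = (1.25 + 1.5c)/3.5.
2. Visits 0 to 18 months, free intercept: time deviations are −0.75, −0.25, 0.25 and 0.75, giving (−0.125 + 0.25 + 0.75c)/1.25 = (0.125 + 0.75c)/1.25.
3. Post-baseline visits, free intercept: deviations are −0.5, 0 and 0.5, giving (−0.25 + 0.5c)/0.5 = c − 0.5.

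| Month-18 course | c | Version 1 | Version 2 | Version 3 |
|---|---|---|---|---|
| Same divergence continues | 1.5 | 1.00 | 1.00 | 1.00 |
| Gap maintained | 1 | 0.79 | 0.70 | 0.50 |
| Half the gap lost | 0.5 | 0.57 | 0.40 | 0.00 |
| All the gap lost | 0 | 0.36 | 0.10 | −0.50 |

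With D = 1.23 points per year, the maintained case gives 1.23 × 0.786 = 0.97, 1.23 × 0.70 = 0.86 and 1.23 × 0.50 = 0.615 points per year. Generalised least squares with a random slope gave the same ratios for random-slope SDs from 0 to 1.9 and residual SDs from 0.5 to 1.4.

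**After the fix.**

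- Data to month 12 only: version 1 becomes (0.25 + 1)/(0.25 + 1) = 1.00, whatever c is.
- Knot at 12 months, arms equal at baseline: the difference is b₁t + b₂·max(t − 1, 0). Months 6 and 12 give b₁ = 1. Month 18 gives 1.5 + 0.5b₂ = c, so the 12-18 month slope difference is b₁ + b₂ = 2c − 2. This is zero when the gap is maintained and negative when it fades. The two questions come apart.

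**The case against.** **The window is inferred.** The article does not say in words that month 18 enters the slope model, and a fuller document could end it at month 12. This stands as a limit on certainty. The inference is still the natural one: the slope model is described as similar to an MMRM over the post-baseline visits, MDS-UPDRS is collected at Day 547, and no cut-off is given.

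**An 18-month slope by randomised arm is a legitimate summary.** The article says only that the model assesses the slope of change over time. Dilution is therefore relative to the on-treatment slope difference, not to every possible target. But a blended slope answers neither of the Overview's two questions, and the nominal-visit MMRM already supplies a month-18 contrast.

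**The periods are already separated elsewhere.** This is correct. The 12-month ANCOVA, the month-18 comparison and the visit-by-treatment terms keep them apart. A reader might infer that the main efficacy conclusion or the power is compromised; the document does not support that, since neither uses the slope model.

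**Month 18 as the dominant point.** A reader might also infer that month 18 always has the most influence on the slope. It does only when the arms share an origin (2.25/3.5 = 64% of the weight). With a free intercept it ties with the earliest visit in the fit.

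**The remedies have limits.** Stopping at Day 365 leaves two post-baseline visits to support a random slope. A knot with a free treatment intercept has three treatment parameters for three post-baseline visits, which reproduces the mean structure of the planned nominal-visit MMRM. Hence the equal-at-baseline constraint in the fix.

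**Conclusion.** The point holds for the supportive slope model as written. Its interaction estimates the on-treatment slope difference only if the arms diverge at an unchanged rate after treatment ends. If the 12-month gap is just maintained, the interaction is 21%, 30% or 50% too small, depending on how the intercept and baseline are handled. If the gap fades the shortfall grows, and in the post-baseline, free-intercept version it reaches zero when half the gap is lost and changes sign when all is lost.

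This rests on three assumptions: that month 18 is in the model, that the on-treatment difference grows linearly, and that the month-18 course is one of those tabulated. The size is therefore a range, not a prediction. The matter is worth settling before unblinding, but it does not touch the trial's primary inference.

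**What to change.** State the window and shape of the slope model, in one of two ways:

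- **Preferred:** a piecewise-linear time effect with a knot at 12 months and the arms constrained equal at baseline, that is, no treatment main effect at time 0. Report separate treatment contrasts for 0-12 months (progression on treatment) and 12-18 months (persistence).
- **Alternative:** keep the single line but restrict the slope model to data up to the Day 365 visit, leaving persistence to the month-18 contrast from the nominal-visit MMRM.

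The cost is a change of wording, with no new data or participants. The on-treatment slope will be somewhat less precise because fewer visits inform it. Under the alternative, the random slope rests on only two post-baseline visits.

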## Ethics and dissemination

This study was approved by the London-Westminster research ethics committee (reference 19/LO/1705) and has been accepted by the MHRA for a clinical trials authorisation (reference CTA 12854/0248/001–0001). In addition, approval has been granted from the Administration of Radioactive Substances Advisory Committee.

We will feedback trial results to participants and our wider cohort of research participants via our annual PD Open Day and newsletter. A lay summary of the results will be available on our website. The results will also be disseminated through publication in scientific journals and presentation at national and international conferences.

AZA-PD has been accepted onto the National Institute for Health Research Clinical Research Network portfolio.
